## 7.2 Treatment Phase

During the treatment of oral etoposide combined with apatinib, patients had to come to outpatient clinic every 3 weeks. When six cycles of oral etoposide in combination with apatinib were completed, apatinib monotherapy was continued and patients had to come to outpatient clinic every one month.

• Laboratory tests including hematology and serum chemistry, and urine routine. Urinary protein quantity in 24 hours will be tested if urinary protein is 2+

• Tumor markers, including CA125, CA199, and HE4.

• Tumor assessment. Tumor response according to RECIST version 1.1 is assessed using computed tomography (CT) or magnetic resonance imaging (MRI) after two, four, and six cycles of oral etoposide, and subsequently every 2 months during apatinib monotherapy until confirmed disease progression.

In case of clinical progression, the date of progression will be defined as the date of the first imaging study that documents progression.

• Adverse events will be reported by the patients and be followed by the investigator until resolution or until a clinically stable endpoint is reached.

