# 5. Treatment and Administration

• Apatinib combined with oral etoposide

• Apatinib, 500 mg, administered orally once daily

• Oral etoposide, 50 mg, administered on days 1 to 14. The administration of oral etoposide will be repeated every 3 weeks for a maximum of six cycles

Treatment was continued until disease progression, patient withdrawal, or unacceptable toxic effects.

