# 6. Dose Modification

## 6.1 Dose Interruptions

Dose interruptions are required on the occurrence of grade 3 or worse toxicities. Treatment has to be delayed until recovery to ≤ grade 2 hematological or ≤ grade 1 nonhematological toxicities. Repeat dose interruptions are allowed for a maximum of 14 days on each occasion.

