# 7. Study Procedures

## 7.1 Screening Phase

Screening procedures to be completed within 30 days before treatment:

• Signed informed consent

• Review of eligibility criteria

• Review of medical history and demographics

• Physical examination

• Vital signs

• Eastern Cooperative Oncology Group (ECOG) performance status

• Laboratory tests including hematology and serum chemistry, and urine routine.

• Tumor markers, including CA125, CA199, and HE4.

• ECG

• Tumor assessments, including radiographic imaging of the chest, abdomen and pelvis by computed tomography (CT) or magnetic resonance imaging (MRI).

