# 8. Efficacy

## 8.1 Evaluations

Measurable disease and the response criteria used in this protocol are defined in the RECIST guidelines (version 1.1) (attachment 1) and will be based on radiologic assessment only.

Appropriate radiological disease assessments (CT scans or MRI) will be performed before treatment, and should include, at a minimum, imaging of the chest, abdomen, and pelvis. Disease will be assessed using CT scans or MRI after two, four, and six cycles of oral etoposide, and subsequently every 2 months during apatinib monotherapy until confirmed disease progression.

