**Specifications by methods of measurements**

*Measurement of lesions*

All measurements should be recorded in metric notation, using calipers if clinically assessed. All baseline evaluations should be performed as close as possible to the treatmentstart and never more than 4 weeks before the beginning of the treatment.

*Method of assessment*

The same method of assessment and the same technique should be used to characterise each identified and reported lesion at baseline and during follow-up. Imaging based evaluation should always be done rather than clinical examination unless the lesion(s) being followed cannot be imaged but are assessable by clinical exam.

*Clinical lesions:* Clinical lesions will only be considered measurable when they are superficial and P10 mm diameter as assessed using calipers (e.g. skin nodules). For the case of skin lesions, documentation by colour photography including a ruler to estimate the size of the lesion is suggested. As noted above, when lesions can be evaluated by both clinical exam and imaging, imaging evaluation should be undertaken since it is more objective and may also be reviewed at the end of the study.

*Chest X-ray:* Chest CT is preferred over chest X-ray, particularly when progression is an important endpoint, since CT is more sensitive than X-ray, particularly in identifying new lesions. However, lesions on chest X-ray may be considered measurable if they are clearly defined and surrounded by aerated lung. See Appendix II for more details.

*CT, MRI:* CT is the best currently available and reproducible method to measure lesions selected for response assessment. This guideline has defined measurability of lesions on CT scan based on the assumption that CT slice thickness is 5 mm or less. As is described in Appendix II, when CT scans have slice thickness greater than 5 mm, the minimum size for a measurable lesion should be twice the slice thickness. MRI is also acceptable in certain situations (e.g. for body scans). More details concerning the use of both CT and MRI for assessment of objective tumour response evaluation are provided in Appendix II.

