**Frequency of tumour re-evaluation**

Frequency of tumour re-evaluation while on treatment should be protocol specific and adapted to the type and schedule of treatment. However, in the context of phase II studies where the beneficial effect of therapy is not known, follow-up every 6–8 weeks (timed to coincide with the end of a cycle) is reasonable. Smaller or greater time intervals than these could be justified in specific regimens or circumstances. The protocol should specify which organ sites are to be evaluated at baseline (usually those most likely to be involved with metastatic disease for the tumour type under study) and how often evaluations are repeated. Normally, all target and non-target sites are evaluated at each assessment. In selected circumstances certain non-target organs may be evaluated less frequently. For example, bone scans may need to be repeated only when complete response is identified in target disease when progression in bone is suspected.

After the end of the treatment, the need for repetitive tumour evaluations depends on whether the trial has as a goal the response rate or the time to an event (progression/death). If ‘time to an event’ (e.g. time to progression, disease-free survival, progression-free survival) is the main endpoint of the study, then routine scheduled re-evaluation of protocol specified sites of disease is warranted. In randomised comparative trials in particular, the scheduled assessments should be performed as identified on a calendar schedule (for example: every 6–8 weeks on treatment or every 3–4 months after treatment) and should not be affected by delays in therapy, drug holidays or any other events that might lead to imbalance in a treatment arm in the timing of disease assessment.

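### The baseline scan window (30 days) conflicts with the 4-week limit in the attached RECIST text, and cycle-linked scans drift with toxicity delays and have no anchor once both drugs stop

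*Protocol*

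**What the plan says.** **Baseline.** Section 7.1 opens with "Screening procedures to be completed within 30 days before treatment", and its list includes CT or MRI of chest, abdomen and pelvis. Section 8.1 states: "Measurable disease and the response criteria used in this protocol are defined in the RECIST guidelines (version 1.1) (attachment 1"). Attachment 1, under the specifications for methods of measurement, wants baseline evaluations close to the start of treatment and "never more than 4 weeks before the beginning of the treatment".

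**On treatment.** Sections 7.2 and 8.1 both place scans "after two, four, and six cycles of oral etoposide, and subsequently every 2 months during apatinib monotherapy until confirmed disease progression". Section 5 fixes the cycle: "The administration of oral etoposide will be repeated every 3 weeks for a maximum of six cycles". Section 6.1 requires interruption at grade 3 or worse and adds: "Repeat dose interruptions are allowed for a maximum of 14 days on each occasion". Section 7.3, on the post-treatment phase, keeps subjects on the schedule until radiographic progression, withdrawal of consent, new anticancer therapy or study termination.

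**Attachment 1 on frequency.** "Frequency of tumour re-evaluation while on treatment should be protocol specific and adapted to the type and schedule of treatment". For phase II it regards 6 to 8 weeks, aligned with cycle ends, as reasonable. It then says that scheduled assessments, above all in randomised comparisons, should follow the calendar "and should not be affected by delays in therapy, drug holidays or any other events" that could unbalance an arm.

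**The concern.** The baseline scan is the reference for partial response, and so for the primary endpoint. Two limits for that scan stand in one document, and a site can comply with section 7.1 while breaching the criteria by which its responses will be judged.

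The on-treatment schedule counts etoposide cycles, not weeks. Patients with more toxicity have longer cycles, are scanned later and have progression recorded later, so PFS and DOR can lengthen as tolerability worsens. Attachment 1 itself notes that these measures depend on how often patients are followed. The schedule also has only two anchors: etoposide cycles and apatinib monotherapy. A patient who stops both drugs before progression has neither, yet section 7.3 expects her to stay on the schedule. PFS is censored at the last disease evaluation, so scans that are never done would become early censoring.

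**Working it through.** **1. Baseline window.** Section 7.1: 30 days. Attachment 1: 4 × 7 = 28 days. Excess: 30 − 28 = 2 days.

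**2. Scan dates.** Inputs: 3-week cycles (section 5), scans after cycles 2, 4 and 6 (section 7.2), at most 14 days (2 weeks) per interruption (section 6.1). Each two-cycle block lasts 2 × 3 = 6 weeks plus any delay.

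| Delay | Block length | Scans at week |
| --- | --- | --- |
| None | 6 | 6, 12, 18 |
| One maximal delay per block | 6 + 2 = 8 | 8, 16, 24 |
| One maximal delay per cycle | 6 + 4 = 10 | 10, 20, 30 |

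The first two rows lie inside Attachment 1's 6 to 8 weeks; the third does not. The third is an assumed worst case with one interruption per cycle. Two months is 2 × 30.4375 / 7 = 8.70 weeks.

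**3. Effect on recorded PFS.** The protocol gives no PFS assumption. I assume exponential time to true progression with median 26 weeks: λ = ln 2 / 26 = 0.02666 per week, 1/λ = 37.51 weeks. With scans D weeks apart, the mean lag from true progression to the detecting scan is

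L(D) = D − [1/λ − D / (exp(λD) − 1)].

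- L(6) = 6 − (37.51 − 34.59) = 3.08
- L(8) = 8 − (37.51 − 33.65) = 4.14
- L(10) = 10 − (37.51 − 32.73) = 5.22
- L(8.70) = 8.70 − (37.51 − 33.33) = 4.52, for the 2-monthly phase

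The first three figures apply only to progressions up to the third scan. The share of progressions by then is F = 1 − exp(−3λD): 0.381, 0.473 and 0.551 for D = 6, 8 and 10. Over all progressions:

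- No slip: 0.381 × 3.08 + 0.619 × 4.52 = 3.97 weeks
- 2-week slip in every block: 0.473 × 4.14 + 0.527 × 4.52 = 4.34 weeks
- 4-week slip in every block: 0.551 × 5.22 + 0.449 × 4.52 = 4.90 weeks

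Increase in mean recorded PFS: 4.34 − 3.97 = 0.37 and 4.90 − 3.97 = 0.93 weeks.

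**4. Sensitivity to the assumed median.** The same formulas give overall lags of 3.74, 4.39 and 5.29 weeks at a median of 13 weeks (increases of 0.65 and 1.55), and 4.14, 4.33 and 4.66 weeks at 52 weeks (increases of 0.19 and 0.52).

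**The case against.** A reader might infer that cycle-linked scanning itself violates the attached RECIST text. The document does not support that. Attachment 1 leaves frequency to the protocol, asks that it suit the treatment schedule, and accepts end-of-cycle scans every 6 to 8 weeks in phase II; the planned 6 weeks fits. Its calendar advice is directed mainly at randomised comparisons, and the stated reason is imbalance between arms, which cannot arise in a single-arm trial. This objection stands in full: the schedule is a weakness, not a contradiction.

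A reader might also infer an upward bias of 1 to 2 weeks in PFS, from 4.14 − 3.08 = 1.06 and 5.22 − 3.08 = 2.14. Those differences cover only progressions up to the third scan. Under the 26-week assumption, 62% of progressions come after week 18 when there is no delay, and the 2-monthly interval then applies whatever happened before.

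The 10-week interval is indeed extreme. Section 6.1 does not say that every interruption moves the etoposide cycle: part of a pause may fall in the week off etoposide, and a pause of apatinib alone need not delay it.

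On stopping, if etoposide alone ends early, the 2-monthly rule for apatinib monotherapy can be read to apply. Section 7.3 also shows the intention to keep scanning after treatment. That intention is clear, but for a patient off both drugs it points to a schedule with no remaining anchor, so this part of the gap stays open.

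On baseline, the defence is only that 2 days is little and that a scan within 28 days satisfies both rules. Both are true; neither removes the conflict.

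**Conclusion.** The baseline conflict is real: 30 days in section 7.1 against 28 in Attachment 1, on the scan that anchors the primary endpoint. It is 2 days wide, and its effect on ORR is likely small.

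Cycle-linked scanning is an avoidable weakness. It makes scan dates depend on toxicity (6 weeks becomes 8, or 10 in the worst case) and leaves patients who stop both drugs before progression without a scan date. The bias in mean recorded PFS is about 0.4 to 0.9 weeks at an assumed exponential median of 26 weeks, with every patient slipping 2 or 4 weeks in every block. Since not every patient will slip in every block, this is an upper figure for that median; a shorter true median would raise it and a longer one lower it. It compares means and is not a predicted shift in the Kaplan-Meier median. The bias concerns PFS and DOR, which are secondary and descriptive; no effect of scan delay on ORR has been shown. The censoring consequence for patients off both drugs cannot be sized from the document.

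**What to change.** - **Section 7.1:** require the baseline tumour scan within 28 days before treatment and leave the other screening items at 30 days. Cost: one line of text, and an occasional early scan must be repeated.
- **Sections 7.2 and 8.1:** set scans by calendar from Day 1 at the protocol's own nominal times, weeks 6, 12 and 18 with a window of about 1 week, then every 2 months as already stated. State that this holds regardless of delay or discontinuation of either drug, until radiographic progression or another stopping event listed in section 7.3. Cost: wording only, with about the same number of planned scans, but some scans will not coincide with a delayed clinic visit.

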## 7.3 Post-treatment Phase

The subjects will continue on the schedule until: 1) radiographic disease progression, 2) the subject withdraws consent, 3) the subject begins subsequent anticancer therapy, or 4) the study is terminated. Once the subject discontinue the treatment, drug-related adverse events during treatment or within 30 days of last dose of the study should be recorded.

# 8. Efficacy

## 8.1 Evaluations

Measurable disease and the response criteria used in this protocol are defined in the RECIST guidelines (version 1.1) (attachment 1) and will be based on radiologic assessment only.

Appropriate radiological disease assessments (CT scans or MRI) will be performed before treatment, and should include, at a minimum, imaging of the chest, abdomen, and pelvis. Disease will be assessed using CT scans or MRI after two, four, and six cycles of oral etoposide, and subsequently every 2 months during apatinib monotherapy until confirmed disease progression.

## 8.2 Endpoints

**Primary endpoints**

• Objective response rate (ORR), is defined as confirmed complete response or partial response under RECIST 1.1 criteria.

**Secondary endpoints**

• Progression-free survival (PFS), is defined as the time from registration to the earlier of death or disease progression.

• Overall survival (OS), is defined as the time from registration until death from any cause (or date of censoring).

• Duration of Response (DOR), is defined as the interval between the date of the first documented response by RECIST to the date of first disease progression or death, whichever occurred earlier.

• Disease control rate (DCR), is defined as the percentage of patients who achieved a complete response, a partial response or stable disease.

• Safety will be described according to the frequency of adverse effects that occur in the treatment.

**Exploratory endpoint**

• The association between the areas of adipose tissue measured by CT scans and efficacy

# 9. Safety Evaluations

## 9.1 Adverse Event

An adverse events is any untoward medical occurrence in a clinical study subject administered a medicinal product. An adverse event does not necessarily have a causal relationship with the treatment. An adverse event can therefore be any unfavorable and unintended sign, symptom, or disease temporally associated with the use of a medicinal product, whether or not related to that medicinal product.

This includes any occurrence that is new in onset or aggravated in severity or frequency from the baseline condition, or abnormal results of diagnostic procedures, including laboratory test abnormalities.

## 9.2 Serious Adverse Event

A Serious Adverse Event (SAE) is defined by FDA and NCI as any adverse drug event (experience) occurring at any dose:

• Results in death

• Is life-threatening

• Requires inpatient hospitalization or prolongation of existing hospitalization

• Results in persistent or significant disability/incapacity

• Is a congenital anomaly/birth defect

• Important Medical Event (IME) that may not result in death, be life threatening, or require hospitalization may be considered a serious adverse drug experience when, based upon medical judgment, they may jeopardize the patient or subject and may require medical or surgical intervention to prevent one of the outcomes listed in this definition.

All SAEs occurring during the study must be reported to Institutional Review Board (IRB) with 24 hours of their knowledge of the event. The initial and follow-up reports of a SAE should be made.

## 9.3 Attribution Definitions

An adverse event is considered associated with the use of the drug if the attribution is possible, probable, or very likely by the definitions.

• **Not Related**

An adverse event that is not related to the use of the drug.

**• Doubtful**

An adverse event for which an alternative explanation is more likely, e.g., concomitant drug(s), concomitant disease(s), or the relationship in time suggests that a causal relationship is unlikely.

**• Possible**

An adverse event that might be due to the use of the drug. An alternative explanation, e.g., concomitant drug(s), concomitant disease(s), is inconclusive. The relationship in time is reasonable; therefore, the causal relationship cannot be excluded.

**• Probable**

An adverse event that might be due to the use of the drug. The relationship in time is suggestive (e.g., confirmed by dechallenge). An alternative explanation is less likely, e.g., concomitant drug(s), concomitant disease(s).

**• Very likely**

An adverse event that is listed as a possible adverse reaction and cannot be reasonably explained by an alternative explanation, e.g., concomitant drug(s), concomitant disease(s). The relationship in time is very suggestive.

## 9.4 Safety Analyses

All subjects who have received at least 1 dose of study drug will be included in the safety analysis. All the adverse events should be recorded in CRF and will be graded according to the NCI-CTCAE, Version 4.03. Serious adverse and deaths will be listed. All adverse events resulting in discontinuation of study treatment, dose modification, the interruption of dosing, or a delay in treatment with the study drug will be noted.

# 10. Statistical Analysis Plan

## 10.1 Analysis Populations

### 10.1.1 Definitions of Study Populations

In this study the following three populations will be defined for the analysis.

• Intent-to-Treat (ITT) Population: The ITT population is defined as all patients who are enrolled in the trial.

• Per Protocol (PP) Population: The per protocol population (PP) defines as a subset of the patients who meet all of the trial criteria and are compliant with the protocol and absence of any major protocol violations.

• Safety Population: The safety population includes the enrolled patients who received at least one dose of study drug.

### 10.1.2 Efficacy analysis populations

The efficacy analyses will be based on the ITT population and PP population.

### 10.1.3 Safety analysis population

The safety population will be used for the analysis of all safety parameters.

## 10.2 Methods of Statistical analysis

### 10.2.1 Analysis of primary endpoint

Objective response rate (ORR) is defined as the proportion of patients who have achieved either CR or PR as defined as RECIST (version 1.1). All other patients will be considered non-responders in the analysis. The objective response rate will be summarized (i.e., number of patients (%)) and the 95% Pearson-Clopper confidence interval for the objective response rate will be provided.

### 10.2.2 Analysis of secondary endpoints

Progression-free survival (PFS) is defined as the time from registration to the earlier of death or disease progression. Patients alive without disease progression are censored at the date of last disease evaluation.

Overall survival (OS), is defined as the time from registration until death from any cause (or date of censoring).

Duration of Response (DOR) is defined as the time from the first CR or PR to the first event of disease progression or death.

The Kaplan-Meier method will be used to estimate the distribution of PFS, OS and DOR. The number of events, subjects censored, the estimate of medians and 95%CIs for the medians will be presented.

Disease Control Rate (DCR) is defined as the percentage of patients who achieved CR, PR or SD. The disease control rate will be summarized (i.e., number of patients (%)) and the 95% Pearson-Clopper confidence interval for the disease control rate will be provided.

### 10.2.3 Safety analyses

All patients who received at least one dose of study drug will be included in the safety analysis. The safety parameters to be evaluated are the incidence, intensity, and type of adverse events, and clinical laboratory results. All adverse events and abnormal laboratory variables will be assessed according to the NCI-CTCAE, Version 4.03 grading system. For each adverse event, the percentage of patients who had at least 1 occurrence of the given event will be summarized. Serious adverse events and deaths will be listed. All adverse events resulting in discontinuation of study treatment, dose modification, the interruption of dosing will be summarized.

Descriptive statistics will be used to summarise ECOG performance status.

### 10.2.4 Analysis of exploratory endpoint

The association between adipose tissue (AT) depots, including visceral AT (VAT), subcutaneous AT (SAT), and intermuscular AT (IMAT), and the efficacy will be evaluated.

The areas of VAT, SAT, and IMAT will be measured by CT scan. The relationships between the ORR and the areas of VAT, SAT, and IMAT will be assessed using logistic regressions. The associations between PFS and OS and the areas of VAT, SAT, and IMAT will be assessed using Kaplan-Meier method and log-rank test.

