## 2.3 Exploratory Objective

• Imaging biomarkers for predictive modeling

To evaluate whether the areas of adipose tissue measured by computed tomography (CT) could predict the efficacy of apatinib.

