# 3. Study Design and Sample Size

## 3.1 Study Design

This is a phase 2, single-arm, open-label study conducted at the Sun Yat-sen University Cancer Centre.

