## 10.3 Sample Size Determination

A Simon’s two-stage design is employed with a one-sided α-error of 5% and a power of 80%. The reported data indicated that the highest objective response rate of oral etoposide monotherapy in platinum-resistant ovarian cancer was 26.7%. We expected that the objective response rate for apatinib combined with etoposide would be 50%.

Under these assumptions, eight evaluable patients will be treated in stage one and more than 2 responses are required to continue to stage two. In the second stage, 27 more patients would be enrolled for a total sample size of 35. Overall, if a total of 14 responses or more are observed, the treatment regimen would be considered a success.

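### Minor (exploratory endpoint): Section 10.2.4 uses a grouping-only test on continuous fat areas, costing about 16–21 points of power, and objective 2.3 asks more than one combination arm can answer

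*Protocol*

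**What the plan says.** Section 10.2.4 first says how the exposure is obtained: "The areas of VAT, SAT, and IMAT will be measured by CT scan". There are three depots: visceral, subcutaneous and intermuscular fat.

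For response it says: "The relationships between the ORR and the areas of VAT, SAT, and IMAT will be assessed using logistic regressions". For survival it says: "The associations between PFS and OS and the areas of VAT, SAT, and IMAT will be assessed using Kaplan-Meier method and log-rank test". The protocol gives no grouping rule and no regression model for PFS or OS.

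The purpose is worded in two ways:

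- Section 2.3, under the label of predictive modelling: "To evaluate whether the areas of adipose tissue measured by computed tomography (CT) could predict the efficacy of apatinib".
- Section 8.2, exploratory endpoint: "The association between the areas of adipose tissue measured by CT scans and efficacy".

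Section 3.1 gives the design: "This is a phase 2, single-arm, open-label study". Section 5 gives the one treatment: "Apatinib combined with oral etoposide".

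**The concern.** There are two linked issues, both confined to the exploratory endpoint.

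**The test does not suit the variable.** An area in square centimetres is a continuous measurement. Kaplan-Meier curves and the log-rank test need groups, so the protocol commits the survival analysis to cutting each area. That discards the ordering of patients within each group. With at most 35 patients, and so at most 35 events, the lost information matters. A real association of moderate size is more likely to be missed than it need be.

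**The objective outruns the design.** To show that fat area predicts the effect of apatinib, one must show that the effect differs by fat area, which requires patients who did not receive apatinib. This trial has none, and all patients also receive etoposide. A fat-outcome association seen here could be purely prognostic, or could relate to either drug.

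**Working it through.** **The plan's only sizing figure.** Section 10.3 sizes the trial on ORR: 8 + 27 = 35 patients, continue with at least 3 responses in 8, success with at least 14 in 35. The probability of success is the sum over x = 3 to 8 of b(x; 8, p) × P(Bin(27, p) ≥ 14 − x). At p = 0.267 this gives 0.0455, and at p = 0.50 it gives 0.805. The stated 5% and 80% are reproduced. Nothing is sized for the fat-area analysis. The 35 is used below only as the ceiling on patients and events.

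**Inputs that are assumptions.** The documents do not give these: a two-sided 5% level, a normally distributed area, exponential survival, about 28–35 events (35 if nobody is censored, about 28–29 with uniform censoring), and hazard ratios of 1.5 to 2.0 per SD of area.

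**Why a split loses power.** The log-rank test is the Cox score test with the area replaced by a 0/1 indicator. Both use U²/V, where U sums (covariate − risk-set mean) over events and V sums the risk-set variances. For a normal variable, the correlation with its own median indicator is √(2/π) = 0.798. The squared value is 2/π = 0.64, so for small effects a median split behaves as if about 36% of the events had been thrown away.

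Hand check at a hazard ratio of 1.5 per SD with 35 events:

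- Continuous: ln(1.5) × √35 = 0.405 × 5.916 = 2.40. Power ≈ Φ(2.40 − 1.96) = Φ(0.44) = 67%.
- Median split: 2.40 × 0.798 = 1.91. Power ≈ Φ(1.91 − 1.96) = Φ(−0.05) = 48%.

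The gap is 19 points. This large-sample formula overstates both powers at n = 35, so simulation is used for the levels.

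**Simulated power, n = 35.**

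| HR per SD | Median-split log-rank | Cox, continuous area |
| --- | --- | --- |
| 1.5 | 37–40% | 53–58% |
| 1.65 | 48–55% | 66–75% |
| 1.7 (35 events only) | 58% | 79% |
| 2.0 | 72–78% | 90–93% |

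In each range the lower figure is for about 28–29 events and the higher for 35. The smallest gap is at HR 2.0 with 35 events (93.3 − 77.6 = 15.7). The largest is at HR 1.7 (78.8 − 58.2 = 20.6). A repeat of the simulation moved single entries by up to about 3 points and left the gap at 16–21.

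**Simulated type I error with no true association.** A fixed median split rejects in about 6% of trials, and Cox on the continuous area in about 5.5–6%. The best of five quantile cuts rejects in about 20%, and the best cut anywhere between the 20th and 80th percentiles in about 32%. The last two apply only if the cut is chosen after looking at outcomes.

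**Absolute sensitivity.** By the Schoenfeld formula, the between-group hazard ratio detectable with 80% power after a median split is exp[(1.960 + 0.842)/√(events × 0.25)]. This is 2.58 with 35 events and 3.07 with 25.

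**Objective against design.** Section 2.3 asks about prediction and names apatinib alone. Sections 3.1 and 5 provide one arm on two drugs. A fat-by-treatment interaction cannot be estimated without a comparator. The apatinib monotherapy phase in Section 7.2 does not supply one, because only patients still on treatment after six cycles reach it. Sections 8.2 and 10.2.4 speak of association with efficacy, which one arm can address.

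**The case against.** The strongest reply is that this is an exploratory marker and that a grouping rule is the sort of detail a separate SAP supplies. That stands: the absence of a cut-point from the protocol is not the point made here. But the protocol itself names the test. A SAP that kept to it could fix the cut and still could not recover the lost information.

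Second, a pre-fixed median split is a valid test, with an error rate essentially the same as Cox. That also stands; the loss is of efficiency only.

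Third, the power figures rest on assumed effect sizes, event counts and distributions, and the protocol sets no power target for this endpoint. This stands for the levels, which is why a range is shown. The gap is much steadier than the levels. Cox does not remove low power either: it reaches only 53–58% at a hazard ratio of 1.5 per SD. If the true relation were a step at the median, the split would lose nothing.

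Fourth, the endpoint and analysis sections already say association. This stands, and confines the wording problem to Section 2.3.

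**Conclusion.** The point holds as a cheap, minor improvement. As written, Section 10.2.4 gives up about 16–21 points of power at n = 35, on the assumptions listed above. Section 2.3 sets an aim that a single arm on two drugs cannot meet, although the endpoint in Section 8.2 can be met.

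Three stronger readings are tempting, and the documents do not support them:

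- **That the plan has a false-positive rate of about 32%.** That figure belongs to a cut chosen from the data. The protocol neither states nor excludes such a choice.
- **That the response and survival analyses use different exposures.** Logistic regression accepts a continuous or a dichotomised area, and Section 10.2.4 does not say which is meant. A mismatch is conjecture.
- **That nine tests share the fault.** Three depots by two time-to-event endpoints give six log-rank tests. The three logistic analyses of ORR are not affected.

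Nothing here touches the ORR decision rule, the secondary efficacy estimates or safety.

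**What to change.** In Section 10.2.4, analyse PFS and OS by Cox regression with each baseline area as a continuous covariate, and report the hazard ratio per SD with its 95% confidence interval. Keep Kaplan-Meier curves by median split for display only. Saying baseline also settles which scan is used, which that section does not name.

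In Section 2.3, align the objective with the endpoint in Section 8.2: the association of baseline adipose area with outcome on apatinib plus etoposide.

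The cost is a few words and a different procedure call, with no added patients, scans or visits. The one statistical price is an assumption that the log hazard is linear in area, which can be checked with residuals.
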